| 5           | to assess behavioural outcomes including smoking, psychological outcomes including cancer worry, anxiety, depression, distress specific to clinical investigations;         | scores at baseline, and follow-up on EQ5D, Hospital Anxiety and Depression Scale (HADS), Positive and Negative Affect Schedule (PANAS), Revised Illness Perception Questionnaire – Lung Cancer (IPQ-LC), Lung cancer risk perception, Health anxiety subscale of Health Orientation Scale (HOS) and the Lung Cancer Worry Scale (LCWS), Medication, smoking behaviour, demographic details. Follow-up questionnaires include same items, plus Impact of Events Scale (intervention group only), healthcare utilisation and dates and results of follow-up investigations for lung cancer (test positive group only). The HADS is not included in follow-up questionnaires. Follow-up questionnaires are administered between 1 and 24 months to subsets of the control arm and intervention arm; |

|          |                                                                                                                                                                                  |                                                                                                                                                                                                                                                                                                                                                           |
|----------|----------------------------------------------------------------------------------------------------------------------------------------------------------------------------------|-----------------------------------------------------------------------------------------------------------------------------------------------------------------------------------------------------------------------------------------------------------------------------------------------------------------------------------------------------------|

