### **1.5.2 Secondary Outcomes**

- 1) numbers, at 24 months after randomisation, in the different stages at diagnosis (3/ 4/ U/ other) in the intervention arm and the control arm;
- 2) difference, after 2 years, between costs and outcomes in the intervention arm and in the control arm, cost-effectiveness of EarlyCDT-Lung test compared to normal clinical practice;
- 3a) estimates, after 2 years, of lung cancer mortality, all-cause mortality and cancer-specific mortality rates in the intervention arm and in the control arm; assessment of significance of differences;
- 3b) estimates, after 5 years and 10 years of long-term future mortality rates in the intervention arm and in the control arm; assessment of significance of differences;
- 4) estimates, after 2 years of (i) the number of patients with stage 3, 4 or unclassified lung cancer at diagnosis in the EarlyCDT-Lung test-positive group and those in the

EarlyCDT-Lung test-negative group and (ii) stage at diagnosis in the EarlyCDT-Lung test-positive and EarlyCDT-Lung test-negative group;

5) scores at baseline, and follow-up on in a survey administered prior to treatment allocation, including EQ5D, , Positive and Negative Affect Schedule (PANAS), Revised Illness Perception Questionnaire – Lung Cancer (IPQ-LC), Lung cancer risk perception, Health anxiety subscale of Health Orientation Scale (HOS) and the Lung Cancer Worry Scale (LCWS), Medication, smoking behaviour, demographic details. Follow-up questionnaires include same items, plus Impact of Events Scale (intervention group only), healthcare utilisation and dates and results of follow-up investigations for lung cancer (test positive group only). The HADS is not included in follow-up questionnaires. Follow-up questionnaires are EQ-5D, cancer worry, positive and negative mood, smoking behaviour including cessation intentions and attempts; scores in additional questionnaires administered at between 1 and 24 months to subsets of the control arm and intervention arm; (all participants in the EarlyCDT-positive group will be approached with the recruitment aim of 300 from this group collected at 1,3,6,12,18 and 24 months. The EarlyCDT-negative and control groups will be recruited at the same rate as the EarlyCDT-positive group with the recruitment aim of 300 from each group collected at 1,3,6 and 12 months).

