| CT Scan*                                                                                                                | X                       | X                                                                                                                   | X                    | X                                                                                                                                                                            | X         |
| *Scheduled every 6 months, if participant enters NHS clinical care pathway, subsequent study CTscans will be cancelled. |                         | Research team member will call 2-4 days before each scheduled CT scan to check health status and attendance. |                      |                                                                                                                                                                              |           |

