written to, explaining the test results and will be offered a follow-up visit or a telephone call if they wish. They will be advised of symptoms to watch for including persistent cough, coughing up blood, shortness of breath, weight loss or loss of appetite. They will be counselled to carry on having tests for other types of cancer if they are offered (e.g. bowel cancer test, mammograms, cervical smears).

Those in the control arm will be written to and thanked for their contribution to the study and advised and counselled identically to those with a negative test result.

All participants who agreed to donate blood for future will be advised that it will be used in cancer related research.

A patient specific section of the study website ([www.eclsstudy.org](http://www.eclsstudy.org)) containing Participant Information Sheets and research staff contact details will be available for participants to view.

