## **4.7 MANAGEMENT OF THE VISITS**

Based on the test's 93% specificity and 41% sensitivity we anticipate that 400-450 participants in the intervention arm will have a positive test result. These will be offered a chest X-ray. Those with a negative or indeterminate X-ray will be referred for a CT scan. If the initial CT is negative then subsequent CTs will be offered 6 monthly for 24 months. Participants will receive appointments via mail/email (as preferred). Participants will be called 2-4 days before each CT-scan appointment. By calling, this allows the participant to ask any questions, check health status, arrange transport (if required) and increase participant retention. Individuals with monitorable abnormalities as classified by the radiology/respiratory physician's study panel on baseline CT scan or subsequent CT will be followed up over the study period or referred for NHS clinical care as appropriate. All individuals entering the study will be flagged and followed-up via the Scottish Cancer Registry. Participants who develop lung cancer will be individually followed-up via their medical records to assess both time to diagnosis and stage of disease at diagnosis. If no histological stage is available, stage will be assessed by a panel of three respiratory physicians blind to allocation status of the study subjects from chest X-rays or CT, or, if no imaging is available, medical assessment of stage will be carried out.

Prior to sending CT scan appointments participant deaths will be checked using the SMR to ensure sensitivity is maintained. All participants in the EarlyCDT- Positive test groups known to have died will be removed from the CT scan appointment schedule register. If patients (EarlyCDT-Positive test) fail to attend for any imaging

assessment during the study, they will receive two reminders (one letter, one phone call). On the third non-attendance, a letter will be sent to the participant's GP to inform them of non-attendance. An appointment window of  $\pm 4$  weeks will be initiated for each scheduled CT scan.

Participants will receive results letters in relation to their initial CXR and CT scan and subsequent CT scans. Any clinical intervention/treatment will be arranged by the study team.

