## **5.1 SAFETY ASSESSMENTS**

As the study does not employ an Investigational Medicinal Product, Adverse Events (AE) or Serious Adverse Events (SAE) will be recorded but not reported in the Annual Report. A number of factors affecting the trial population suggest that we would expect to observe a larger than normal incidence of episodes of ill-health due to both the age and co-morbidities of the study population. All known disease progressions and co-morbidities will be regarded as outcomes including complications arising from investigations which result in a hospital stay which will be captured in outcome 6 and all medical treatment or interventions will be predicated upon normal clinical care and not related to the study protocol. All CXR and CT scan incidental findings (incidentaloma) will be recorded in the CRF as an incidental finding and a specialist referral will be made as directed in a study SOP within the Study Operations Manual. AEs (as defined) will be recorded as soon as they are known either from the study subjects, PI patient review audits or via SMR or record review.

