## **6 DATA COLLECTION & MANAGEMENT**

### **6.1 DATA COLLECTION**

It is the CI and PIs responsibility to ensure the accuracy of all data entered and recorded in the CRF/eCRFs and the database. The Delegation of Responsibilities Log will identify all trial personnel responsible for data collection, entry, handling and managing the database.

The data will be collected by the RN and/or the PI either directly onto a paper CRF with subsequent transcription to the eCRF, or direct data entry onto the web based eCRF. Where there is electronic storage of non-identifiable data this will be on a password protected device and/or database. A plan for data quality control will be developed by the data management staff at Tayside Clinical Trials Unit and the trial management team.

All research blood samples (anonymised using barcodes) will be labelled and packaged according to IATA regulations using Royal Mail Safeboxes or INTELSIUS or equivalent transport box systems to be transported to the University of Nottingham for processing, transporting and storage of samples for future research. All samples will be stored under custodianship as per UK Biobank guidelines. Sample Analysis and Chain of Custody Plans will be documented in the Study Operations Manual. The participant's medical notes (GP and hospital) paper or electronic will act as source data for relevant past medical history, subsequent medical conditions, hospital admissions and diagnostic reports.

Psychological and behavioural data relating to smoking, psychological outcomes including cancer worry, anxiety, depression and distress will be collected on all 10,000 participants through a baseline questionnaire administered during Visit 1. If required the RN can assist the participant with the completion of the questionnaire. Follow-up data will be collected between 1 and 24 months on subsets of the intervention and control groups. All participants in the EarlyCDT-positive group will be approached with the recruitment aim of 300 from this group collected at 1,3,6,12,18 and 24 months. The EarlyCDT-negative and control groups will be approached at the same rate as the EarlyCDT-positive group with the recruitment aim of 300 from each group, collected at 1,3,6 and 12 months.. A web-based tool will be used weekly to randomly sample patients from the EarlyCDT-negative and control groups, stratified by the two study centres. It is anticipated an average of 8 individuals (4 from each of

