2.4.2 Number of patients who have been lost to follow up

2.4.3 Number of patients with missing follow up data

2.5 Frequency of primary events (if applicable)

3. Did you submit any data for interim analysis of efficacy

Yes/No

4. Analysis of safety data.

These are to be presented overall and by group:

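### Adverse events are recorded as they become known, and test-positives are contacted far more than anyone else, so by-group counts that include contact-derived events may show a spurious excess in the intervention arm

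*Protocol*

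**What the plan says.** Section 5.1 sets no enquiry schedule for adverse events. They are to be "recorded as soon as they are known either from the study subjects, PI patient review audits or via SMR or record review". The section fixes no enquiry common to all groups and does not ask for the source of each event to be noted.

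Contact after Visit 1 differs by group:

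- **Test-positives** have a results visit or call and a chest X-ray (2.2, 2.4), then study CTs: "If the initial CT is negative then subsequent CTs will be offered 6 monthly for 24 months" (4.7). Table 1 in 2.4 adds: "Research team member will call 2-4 days before each scheduled CT scan to check health status and attendance". The flowchart in 2.2 has the PI see those with a positive or suspicious X-ray if required.
- **Test-negatives** get a results letter, with a visit or call if they want one (4.1).
- **Controls**: "Those in the control arm will be written to and thanked for their contribution to the study" (4.1), with the same advice as test-negatives.
- **Samples of test-negatives and controls** get follow-up questionnaires, "with the recruitment aim of 300 from each group, collected at 1,3,6 and 12 months" (6.1). The outcomes summary says these repeat the baseline items, "plus Impact of Events Scale (intervention group only), healthcare utilisation". Test-positives are also surveyed at 18 and 24 months.

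Appendix 3, DMEC Report Template 2, item 4 covers serious adverse events and other adverse events: "These are to be presented overall and by group". The same appendix has the DMEC discuss adverse-event data and advise the TSC on whether the trial should continue.

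Some capture does not depend on arm. The flowchart in 2.2 collects deaths, morbidity and hospitalisations for every participant. Section 5.1 sends investigation complications with a hospital stay to outcome 6, which comes from SMR linkage. Section 6.1 names GP and hospital notes as source data for later conditions, without limit by arm.

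**The concern.** A between-arm comparison of harms is interpretable only if events have the same chance of being found in each arm. Here two of the four sources, the participant's own report and PI review, operate chiefly in one subgroup of one arm. Their yield is pooled with linkage and record review, and the pooled count goes into a by-group table. Such a table partly measures how often people were spoken to.

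This matters because weighing potential harm against benefit is a stated purpose of the trial (Design, and How the results will be used), and because the DMEC's advice draws partly on adverse-event data. Minor complications of imaging and work-up without a hospital stay are not routed to outcome 6, so they depend on the adverse-event route. A later analysis cannot recover control events that were never recorded. Nor can it separate contact-derived events from the rest if the source was not noted.

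**Working it through.** **Inputs**

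- Group size: 5,000 per arm (7.1).
- Expected test-positives: 400-450 (4.7).
- Study CTs: 0, 6, 12, 18 and 24 months, so up to 5, each preceded by a call (2.4).
- Questionnaire samples: aim of 300 controls and 300 test-negatives, at 4 time points (6.1).
- Capture ratio k: the chance that an event is recorded in a test-positive divided by the chance in everyone else. The Protocol gives no adverse-event or capture rate, so k is an assumption.

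**Step 1. The plan's own figures.** A two-proportion calculation for 2.4% against 1.56% with 85% power at two-sided 5% gives 4,938 per group, and 5,000 per group gives 85.4% power, so the denominator reproduces. Expected positives are 5,000 × (0.41p + 0.07(1 − p)), where p is the proportion with lung cancer. This gives 384 at p = 2%, 401 at 3%, 418 at 4% and 450 at 5.9%. The stated 400-450 is therefore reproduced for p of about 3% to 5.9%.

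**Step 2. Share of the arm with the extra contact.** f = 400/5,000 = 0.08 to 450/5,000 = 0.09.

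**Step 3. Scheduled contacts.** Pre-scan calls: 400 × 5 = 2,000 to 450 × 5 = 2,250 in the intervention arm. This is a ceiling, because study CTs are cancelled when a participant enters NHS care. Controls have no such calls, but the sampled controls (300/5,000 = 6%) can return up to 300 × 4 = 1,200 questionnaires.

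**Step 4. Recorded ratio with equal true rates.** Recorded ratio, intervention to control = 1 + f(k − 1).

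| k (assumed) | f = 0.08 | f = 0.09 |
|---|---|---|
| 1 | 1.00 | 1.00 |
| 1.5 | 1.04 | 1.045 |
| 2 | 1.08 | 1.09 |
| 3 | 1.16 | 1.18 |
| 5 | 1.32 | 1.36 |

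In a direct comparison of test-positives with controls there is no dilution, and the recorded ratio is k itself.

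**Step 5. Do the questionnaires even things out?** Take 425 positives (f = 0.085), k = 2, and suppose that a questionnaire also doubles capture in the sampled 6% of each arm. Intervention: 0.085 × 2 + 0.06 × 2 + 0.855 = 1.145. Control: 0.06 × 2 + 0.94 = 1.06. Ratio: 1.145/1.06 = 1.08, against 1.085 without the questionnaires. They hardly change it.

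**Step 6. Which events have k above 1?** Deaths and hospitalisations are collected for everyone, so k is about 1 for them, and they make up most of what the DMEC template defines as serious. A non-admitted event that a GP has noted can be found in either arm if record review is run alike. The remainder is mainly non-serious events that reach neither SMR nor the notes.

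**The case against.** The case against is substantial, and much of it stands.

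- **Controls are not without contact.** A reader might infer from the calls alone that they are. The Protocol plans questionnaires covering healthcare use for about 300 of them. This corrects the description, but Step 5 shows that it does not remove the imbalance.
- **Most serious harm is already captured alike.** Deaths, admissions and outcome 6 do not depend on study contact, and GP notes can reveal non-admitted events in either arm. This stands and sets the scope of the point. However, 5.1 lists record review only as one of several routes. It does not say that it is run the same way for everyone, or that a between-arm table is limited to it and linkage.
- **No test on adverse-event counts is planned.** A reader might go on to calculate a chance of a falsely significant excess. The Protocol sets no significance test or stopping boundary for these counts, and such a figure would need an invented capture ratio and an invented event count. None is given here.
- **The DMEC template is generic.** It speaks of doses and trial medications, and Appendix 3 leaves the reported material to agreement at the first meeting. So the table may change, and it is not by itself decisive. As written, though, it asks for both kinds of event by group, and it cannot be split by source later unless 5.1 has the source recorded.
- **Outcome 7.** The questionnaire also asks for "dates and results of follow-up investigations for lung cancer (test positive group only" (1.5.2). A reader might infer that this biases the counts of investigations in outcome 7. Nothing in the Protocol says that the item feeds outcome 7, so the inference is not supported.

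**Conclusion.** The point holds in limited form. Ascertainment of adverse events is unequal by design, and the Protocol places the pooled result in a by-group safety table. The direction follows from the contact schedule: any excess from this source would appear in the intervention arm.

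The size is uncertain and probably modest over the whole arm. It reaches only the 8-9% who test positive, and mainly events that are neither serious nor hospitalised and are absent from SMR and the notes. The ratio of 1.08-1.09 for doubled capture is an illustration that rests on an assumed k.

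It would go too far to conclude that the intervention will look more harmful. The documents support only that counts including contact-derived events may show a spurious excess. No figure in the sample size calculation is affected.

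**What to change.** In 5.1 and in item 4 of the second DMEC report template:

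1. Record the source of each adverse event: participant contact, PI review, SMR linkage or record review.
2. Base any between-arm comparison of adverse events only on those found by SMR linkage or record review, run identically over the same 24-month window for all randomised participants.
3. List events learned through study visits, pre-scan calls or PI review separately for the test-positive group, with no control column.

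With sources that do not depend on arm, k = 1 and the expected recorded ratio under equal true rates returns to 1.00.

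The cost is a short wording change, a source field on the adverse-event form and a revised table shell. SMR linkage is already planned; record review must be done alike for everyone if its events are to be compared. The downside is that minor contact-derived events are described but not compared between arms.

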## **6 DATA COLLECTION & MANAGEMENT**

### **6.1 DATA COLLECTION**

It is the CI and PIs responsibility to ensure the accuracy of all data entered and recorded in the CRF/eCRFs and the database. The Delegation of Responsibilities Log will identify all trial personnel responsible for data collection, entry, handling and managing the database.

The data will be collected by the RN and/or the PI either directly onto a paper CRF with subsequent transcription to the eCRF, or direct data entry onto the web based eCRF. Where there is electronic storage of non-identifiable data this will be on a password protected device and/or database. A plan for data quality control will be developed by the data management staff at Tayside Clinical Trials Unit and the trial management team.

All research blood samples (anonymised using barcodes) will be labelled and packaged according to IATA regulations using Royal Mail Safeboxes or INTELSIUS or equivalent transport box systems to be transported to the University of Nottingham for processing, transporting and storage of samples for future research. All samples will be stored under custodianship as per UK Biobank guidelines. Sample Analysis and Chain of Custody Plans will be documented in the Study Operations Manual. The participant's medical notes (GP and hospital) paper or electronic will act as source data for relevant past medical history, subsequent medical conditions, hospital admissions and diagnostic reports.

Psychological and behavioural data relating to smoking, psychological outcomes including cancer worry, anxiety, depression and distress will be collected on all 10,000 participants through a baseline questionnaire administered during Visit 1. If required the RN can assist the participant with the completion of the questionnaire. Follow-up data will be collected between 1 and 24 months on subsets of the intervention and control groups. All participants in the EarlyCDT-positive group will be approached with the recruitment aim of 300 from this group collected at 1,3,6,12,18 and 24 months. The EarlyCDT-negative and control groups will be approached at the same rate as the EarlyCDT-positive group with the recruitment aim of 300 from each group, collected at 1,3,6 and 12 months.. A web-based tool will be used weekly to randomly sample patients from the EarlyCDT-negative and control groups, stratified by the two study centres. It is anticipated an average of 8 individuals (4 from each of

the two study centres) will be randomly sampled and invited to complete follow-up questionnaires from each of the EarlyCDT-negative and control groups per week (based on a 10 month recruitment period and an anticipated response rate of 67%). Response rates will be monitored and if they are lower than 67%, the number randomly sampled at each centre will be increased to achieve a minimum of 200 responses. Participants will be sent a £5 gift voucher for use in a range of stores for each questionnaire to be completed. A Cochrane review found the use of small monetary incentives significantly increases response rates to postal questionnaires (Edwards et al., 2009). There are precedents in trials and other UK studies where small monetary incentives have been used.

Two methods will be used for the initial period of recruitment: 50% of the sample will receive the questionnaire with the voucher and 50% will receive the voucher once they have returned their questionnaire. An assessment will be carried out to determine which of the two methods is more effective in maximising recruitment rate and will then be employed for the remainder of the study. .

A phone number will be provided for participants to call the research team for assistance in completing questionnaires. Occasionally the research team may call participants to check on postal delivery and offer assistance with completion to increase return rate. Participants who develop lung cancer during the 24 month follow-up period will not be sent further study questionnaires.

